## Abstract

**Background:**

Patients having arthroscopic shoulder surgery frequently experience periods of inadvertent hypothermia. This common perioperative problem has been linked to adverse patient outcomes such as myocardial ischaemia, surgical site infection and coagulopathy. International perioperative guidelines recommend patient warming, using a forced air warming device, and the use of warmed intraoperative irrigation solutions for the prevention of hypothermia in at-risk patient groups. This trial will investigate the effect of these interventions on patients’ temperature, thermal comfort, and total recovery time.

**Method/Design:**

The trial will employ a randomised 2 x 2 factorial design. Eligible patients will be stratified by anaesthetist and block randomised into one of four groups: Group one will receive preoperative warming with a forced air warming device; group two will receive warmed intraoperative irrigation solutions; group three will receive both preoperative warming and warmed intraoperative irrigation solutions; and group four will receive neither intervention. Participants in all four groups will receive active intraoperative warming with a forced air warming device. The primary outcome measures are postoperative temperature, thermal comfort, and total recovery time. Primary outcomes will undergo a two-way analysis of variance controlling for covariants such as operating room ambient temperature and volume of intraoperative irrigation solution.

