### Outcomes

The primary outcome measure in this trial is postoperative temperature. The secondary outcomes of interest are thermal comfort and total recovery time. Baseline data on patient temperature and thermal comfort will be collected on arrival into the department (T_0_). Follow-up measures will be collected at four time points; immediately prior to induction (T_1_), on arrival into the recovery unit (T_2_), 20 minutes after arrival into the recovery unit (T_3_) and immediately prior to discharge from the recovery unit (T_4_) (see Figure 1).

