### Sample size

The trial has been powered to detect a 0.05°C (SD 0.5) difference in temperature between the four study groups. This was deemed a clinically significant difference based on the researchers experience and previous published studies [12,24]. Based on this number, and given the trial’s design, a total sample size of 120 participants is required to power the trial at 80% with a significance level of 5%.

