### Statistical analysis

Intention-to-treat analysis will be applied. Data will be analysed according to the 2x2 randomised factorial study design. The two-way analysis of covariance (two-way ANCOVA) will be used for the primary and secondary outcome measures of temperature, thermal comfort and total recovery time. The two-way ANCOVA model will also include operating room ambient temperature, volume of irrigation solution, length of surgery, blood loss and other covariates identified in the bivariate analyses. The analysis will be adjusted for baseline temperature and thermal comfort. Pair-wise comparison between groups will be conducted based on the results obtained from the two-way ANCOVA.

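### The Abstract names three primary outcomes and the Methods name one, so the criterion for a positive trial is contradictory

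*Protocol article*

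**What the plan says.** The protocol article gives two rankings of the same three outcomes.

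- Abstract, Method/Design: "The primary outcome measures are postoperative temperature, thermal comfort, and total recovery time". The following sentence keeps the plural: "Primary outcomes will undergo a two-way analysis of variance".
- Methods, Outcomes: "The primary outcome measure in this trial is postoperative temperature. The secondary outcomes of interest are thermal comfort and total recovery time".

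Other sections bear on the ranking without settling it in words:

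- Sample size is calculated for temperature only: "The trial has been powered to detect a 0.05°C (SD 0.5) difference in temperature between the four study groups". The total is 120 at 80% power and 5% significance.
- Statistical analysis says that the two-way ANCOVA "will be used for the primary and secondary outcome measures of temperature, thermal comfort and total recovery time". This presupposes a primary and a secondary tier, but does not say which outcome belongs to which.
- Interim analysis plans one efficacy look at 75% enrolment with O'Brien-Fleming boundaries and an overall level of 0.05. It names no outcome.
- Purpose lists the three outcomes without ranking them, and the Discussion rests the trial's novelty on comfort and recovery time.

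**The concern.** The primary outcome decides what counts as a positive trial. Suppose temperature shows no effect and recovery time does. A reader of the Abstract could call that a positive primary result; a reader of the Methods could not. The choice between the two would then be open after the data are seen.

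The ambiguity also reaches the interim look. That section does not say which outcome is compared with the boundary, so a reader would take it to be the primary one. Under the Abstract that means three outcomes, and under the Methods one.

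Finally, the article gives no power for thermal comfort or total recovery time. That is normal for secondary outcomes, but it does not fit outcomes called primary.

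**Working it through.** **Side by side.** The Abstract counts three primary outcomes. The Outcomes section counts one primary and two secondary. Neither text is an amendment log, and each is a complete sentence, so neither condensing nor text extraction explains the difference. The temperature-only sample size and the two-tier wording of the Statistical analysis section agree with the Outcomes section. No section of the Methods supports three primaries.

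**The plan's own figure.** With a difference of 0.05 °C and SD 0.5, two-sided 5% (sidedness assumed) and 80% power, a main effect needs

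n per level = 2 × (1.960 + 0.842)² × 0.5² / 0.05² ≈ 1,570, or 3,140 in total.

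The stated 120 does not reproduce. That is a separate matter, and nothing below depends on it. What matters here is that the calculation covers temperature and nothing else.

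**What each reading would do to the error rate**, per factorial effect (one intervention against its absence):

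1. One primary outcome at 0.05: the false-positive chance is 5%.
2. Three primaries, any one sufficient, each at 0.05. The any-one rule and the level per outcome are assumptions, because the article states neither.
   - Independent outcomes: 1 − (1 − 0.05)³ = 1 − 0.857375 = 14.3%.
   - Correlated outcomes, by simulation of three two-sided z tests (correlations assumed, because the article gives none): 13.6% at 0.3, 12.5% at 0.5, 9.8% at 0.8.
   - Holding 5% by Bonferroni would need 0.05 / 3 = 0.0167 per outcome.
3. Three primaries, all required. The false-positive chance stays at or below 5%. Joint power would be 0.8³ = 51% if each outcome had 80% power and they were independent. Both conditions are assumed, because the article gives no power for comfort or recovery time.

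**Both factors together.** Treating the two interventions as one family and all tests as independent, three outcomes give 1 − 0.95⁶ = 26.5%. Temperature alone already gives 1 − 0.95² = 9.75%. The fair contrast is therefore 26.5% with 9.75%, not with 5%.

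**The case against.** The strongest reply is that the operative text already settles the ranking. The Outcomes section is explicit, the sample size follows it, and the Statistical analysis section keeps two tiers. The Abstract is a summary and the lone outlier. This stands as the reason for choosing the Methods as the reference. It lowers the practical risk, but it does not remove two opposing statements about the primary outcome.

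Three stronger readings are tempting, and the article does not support them.

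- A reader might infer that the article states contradictory error rates. It states one, 5%, under Sample size and again under Interim analysis. The conflict is in the outcome labels; any inflation is a consequence under one reading.
- A reader might infer that the Abstract tests each of three primaries at an unadjusted 5%. The Abstract gives no significance level. A missing multiplicity rule is also something that an article may leave to an analysis plan that is not shown, so the absence is not a fault in itself.
- A reader might set about 24 to 27% over both factors against 5%. Part of that comes from testing two interventions, and would remain with a single primary outcome.

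It is also fair to say that aligning the labels does not identify which postoperative time point is primary. That lies outside this point.

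**Conclusion.** The contradiction holds. As published, the criterion for a positive trial differs between the Abstract and the Methods, and the body of the article favours one primary outcome, postoperative temperature.

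The contradiction itself needs no assumption. Its numerical size does. The 14.3% per factorial effect requires the Abstract's ranking, success on any one outcome, 5% for each, and independence. With positive correlation it is lower: about 12.5% at 0.5 and 9.8% at 0.8. Under the Methods' ranking it is 5%. If all three outcomes were required, the cost would fall on power and not on the error rate.

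**What to change.** Two edits:

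1. In the Abstract, name postoperative temperature as the single primary outcome and list thermal comfort and total recovery time as secondary. Adjust the next sentence, which speaks of several primary outcomes.
2. Under Interim analysis, state that the O'Brien-Fleming boundary applies to the primary outcome.

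Neither edit changes the sample size, the significance level or the trial's procedures. The cost is that no primary claim can be made on thermal comfort or recovery time, the two outcomes on which the Discussion bases the trial's novelty; results on them would be reported as secondary.

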**Discussion:**

This trial is designed to confirm the effectiveness of these interventions at maintaining perioperative normothermia and to evaluate if this translates into improved patient outcomes.

**Australian New Zealand Clinical Trials Registry number:**

ACTRN12610000591055

## Background

Inadvertent perioperative hypothermia, defined as a core temperature below 36°C [1], is a common, yet widely under-acknowledged adverse clinical consequence of surgery [1-3]. Patients undergoing arthroscopic shoulder surgery are particularly at risk, with the average patient experiencing a core temperature heat loss of between 1°C and 3°C [4-6]. Three principle factors are said to contribute to this problem: Reduced metabolic heat production due to the anaesthetic; heat loss due to the cold perioperative environment and the use of large quantities of surgical irrigation solution; and impaired thermoregulation which results in a core to periphery thermal redistribution [7].

Although hypothermia is a common perioperative problem, it is not a benign one: The consequences are both physiological and psychological in nature and are far more serious than patients just ‘feeling uncomfortably cold’. Research has demonstrated a clear link between inadvertent perioperative hypothermia and serious adverse complications including myocardial ischaemia, surgical site infection, and coagulopathy [1,8-11]. A person’s temperature is also an integral component of their overall perception of well-being and research has shown that memories of thermal discomfort during the perioperative period significantly affect a patient’s surgical experience [12,13]. These physiological and psychological adverse effects can, and do, result in prolonged recovery times, lengthier hospital stays, and increased resource use which in turn translates into greater overall healthcare costs [10,11].

A number of active and passive interventions are recommended in the evidence-based guidelines for maintaining normothermia in perioperative patients [1,14]. Two relatively simple and inexpensive interventions which are not routinely used on patients undergoing shoulder arthroscopy surgery are preoperative warming using a forced air warming device and the use of warmed intraoperative irrigation solutions [7].

### Preoperative warming

The preoperative warming of patients at high risk of hypothermia, such as those having arthroscopic surgery, is recommended in evidence-based guidelines [1,14]. Warming the peripheral tissues preoperatively reduces the impact of core to periphery thermal redistribution caused by anaesthetic-induced peripheral vasodilatation [15]. Consequently, patients experience less post-induction temperature loss and recover from any loss at a faster rate intraoperatively [16-19]. A forced air warming device has been shown to be the most effective method for preoperative warming, consistently demonstrating higher core temperatures in preoperative normothermic patients compared to other warming techniques [17,19-23].

### Warmed intraoperative irrigation solutions

It is well documented that the use of room temperature irrigation solution increases the risk of inadvertent perioperative hypothermia during arthroscopic surgery. A systematic review of 13 randomised controlled trials including 686 patients showed that room-temperature irrigation fluid caused a greater drop in core body temperature and more episodes of hypothermia in patients, than warmed irrigation fluid [4]. There is a significant correlation between the volume of room temperature irrigation solution used and a patients’ mean postoperative temperature [6,24]. The use of warmed solution for intraoperative irrigation during arthroscopic surgery has been recommended as a method for preventing perioperative hypothermia [1,4,14].

There is clear evidence that these two interventions assist in the maintenance of perioperative normothermia but there is now a call for robust well designed research to demonstrate improved clinical outcomes associated with their use [1]. This trial will study the effects of these warming interventions on outcomes of particular interest to perioperative nurses, namely, post-operative temperature, thermal comfort, and total recovery time.

### Purpose

To investigate the effect of preoperative forced air warming and warmed intraoperative irrigation solution, alone and in combination, on postoperative temperature, thermal comfort, and total recovery time in adult patients undergoing elective arthroscopic shoulder surgery.

## Method

### Trial design

The trial will employ a randomised 2 x 2 factorial design. An equal ratio of participants will be allocated to each group. This design will enable the study of each intervention on the outcome variable, as well as the effects of interactions between interventions on the outcome variable.

### Setting

The trial will be conducted in the day surgery unit of a private hospital in Sydney, Australia.

### Eligibility criteria

Participants will be deemed eligible for the trial if they are over the age of 18 years and are scheduled for elective arthroscopic shoulder surgery. They must be classified as American Society of Anaesthesiologists grade I-III (see Table 1) and have a body mass index between 18.5 and 40. Patients will be excluded if they have a preoperative temperature above 37.5°C or if they are unable to speak or understand English.

**Table 1 T1:** American Society of Anaesthesiologists grading

**ASA**	**Description**
I	Healthy individual with no systemic disease
II	Mild systemic disease not limiting activity
III	Severe systemic disease that limits activity but is not incapacitating
IV	Incapacitating systemic disease which is constantly life-threatening
V	Moribund, not expected to survive 24 hours with or without surgery

### Interventions

Participants will be allocated to one of four groups (see Table 2): Group one will receive preoperative warming with a forced air warming device; group two will receive warmed intraoperative irrigation solutions; group three will receive both preoperative warming and warmed intraoperative irrigation solutions; and group four will comprise the control group receiving neither intervention.

**Table 2 T2:** Interventions allocated to each study group

	**Preoperative warming**	**No preoperative warming**
**Warmed irrigation solutions**	Group 1	Group 2
**No warmed irrigation solutions**	Group 3	Group 4

#### Preoperative forced air warming

Those allocated to group 1 and 3 will be changed into a hospital gown and seated in a recliner chair in the preoperative holding area. A commercial warming blanket will be applied to approximately 50% of their anterior body surface and a hospital sheet placed on top. They will then receive 45 minutes of preoperative forced air warming (Bair Hugger® model number 775) with the device temperature set at 43°C. Participants will be monitored for sweating, flushing and thermal discomfort and the device temperature titrated accordingly.

#### Warmed intraoperative irrigation solution

Patients allocated to group 1 and 2 will have their intraoperative irrigation solutions warmed to 37°C [24] in a thermostatically controlled warming cabinet. The warming cabinet will be located in the operating room in which the solutions will remain until they are required. A process of random quality checks will be instigated to confirm the temperature of the irrigation fluid.

#### Usual care

Participants in group four will receive ‘usual care’ only. This does not include preoperative warming or the use of warmed intraoperative irrigation solutions. All four groups will receive active intraoperative warming with a forced air warming device (Bair Hugger® model number 775) for the duration of their surgery.

### Outcomes

The primary outcome measure in this trial is postoperative temperature. The secondary outcomes of interest are thermal comfort and total recovery time. Baseline data on patient temperature and thermal comfort will be collected on arrival into the department (T_0_). Follow-up measures will be collected at four time points; immediately prior to induction (T_1_), on arrival into the recovery unit (T_2_), 20 minutes after arrival into the recovery unit (T_3_) and immediately prior to discharge from the recovery unit (T_4_) (see Figure 1).

**Figure 1 F1:**
[figure not shown]
Study flow diagram.

#### Temperature

Temperature will be measured by nursing staff using a dedicated tympanic thermometer (Welch Allyn Braun Thermoscan® PRO 4000). This device has been shown to be reliable when tested against readings from a pulmonary artery catheter (the ‘gold standard’ in core temperature assessment) and is deemed more accurate than other similar devices [25]. The thermometer will be calibrated by the clinical engineering department (as per the manufacturer’s instructions). All nursing and medical staff will receive instruction in its use prior to the trial commencing.

#### Thermal comfort

Thermal comfort will be measured on a 10 point self-reported thermal comfort scale. This type of numeric rating scale has been used effectively in other studies on thermal comfort [26,27]. Participants will be asked, using a standardised script, to score how comfortable they are with their body temperature on a scale from 0 to 10 with zero being very comfortable (neither too hot nor cold) and 10 being very uncomfortable (too hot or cold).

#### Total recovery time

Total recovery time will be calculated from the patient’s arrival into the recovery unit until the time they are deemed fit for discharge from the recovery unit by the recovery nurse. Fitness for discharge will be assessed using a standardised post anaesthetic discharge scoring tool (see Table 3) [28].

**Table 3 T3:** Aldrete and Kroulik modified post-anaesthetic recovery score. A total score >8 indicates recovery from anaesthetic

**Variable**		**Score**
Consciousness	Fully awake and oriented (name, place, date)	2
	Awake when called	1
	Not responding	0
Activity	Moves all four extremities on command	2
	Moves two extremities	1
	Unable to move extremities	0
Respiration	Breathes deeply and coughs freely	2
	Dyspnoea, limited breathing, or tachypnoea	1
	Apnoeic	0
Circulation	BP ±20% of pre-anaesthetic level	2
	BP ±20%–50% of pre-anaesthetic level	1
	BP ±50% of pre-anaesthetic level	0
Peripheral oxygen saturation	>92% on room air	2
	>92% with oxygen	1
	<92% with oxygen	0

### Sample size

The trial has been powered to detect a 0.05°C (SD 0.5) difference in temperature between the four study groups. This was deemed a clinically significant difference based on the researchers experience and previous published studies [12,24]. Based on this number, and given the trial’s design, a total sample size of 120 participants is required to power the trial at 80% with a significance level of 5%.

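### The sample size statement is inconsistent: with SD 0.5, 120 participants give about 8% power for a 0.05°C difference, not 80%

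*Protocol article*

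**What the plan says.** The Sample size section of the protocol article states the target as follows: "The trial has been powered to detect a 0.05°C (SD 0.5) difference in temperature between the four study groups". It calls this difference clinically significant, citing the researchers' experience and earlier studies. It then concludes that, on this basis, "a total sample size of 120 participants is required to power the trial at 80% with a significance level of 5" per cent.

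The Trial design section sets equal allocation in a 2 x 2 factorial. That makes 30 participants per cell and 60 per level of each factor. The same section says the design will show the effect of each intervention "as well as the effects of interactions between interventions on the outcome variable". The Statistical analysis section plans a two-way ANCOVA followed by pairwise comparisons between groups. The Outcomes section names postoperative temperature as the primary outcome, so this calculation concerns the primary outcome.

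**The concern.** A difference of 0.05 against an SD of 0.5 is a standardised effect of 0.1. Detecting that with 80% power takes thousands of participants, not 120. The text also speaks of a difference among four groups without saying which contrast it means: a main effect, a comparison of two cells or the interaction. Power at 120 differs widely between these.

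As a supporting sign only, the Background describes arthroscopic shoulder patients "with the average patient experiencing a core temperature heat loss of between 1°C and 3°C". The target of 0.05°C is about 2% to 5% of that fall (0.05/3 and 0.05/1).

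This paragraph is the only justification given for the size of the trial, and it is the benchmark for reading a null result. As written, a reader would take a non-significant result as evidence against an effect as small as 0.05°C. The trial cannot support that reading.

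**Working it through.** **Inputs.** Difference δ = 0.05°C, SD σ = 0.5°C, power 80%, α = 0.05 and N = 120 come from the Sample size section. Equal allocation over four cells comes from Trial design. Sidedness is not stated; two-sided is assumed and one-sided is also tried. The standardised difference is d = 0.05/0.5 = 0.1.

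**Step 1: try to reproduce 120.** Normal approximation, with (1.960 + 0.842)² = 7.849:

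- Main effect: N = 4 × 7.849 / 0.1² = 3,140 in total.
- Two cells: N = 4 cells × 2 × 7.849 / 0.1² = 6,279, so 6,280 in total (1,570 per cell).
- Interaction, taking 0.05°C as a difference of differences: N = 16 × 7.849 / 0.1² = 12,558, about 12,560 in total.
- Main effect, one-sided: 2,474 in total.

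The stated 120 is not reproduced. Even the most favourable case needs 2,474/120, or about 20 times as many.

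**Step 2: power at N = 120.** Noncentral t, two-sided 5%:

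| Contrast | Noncentrality | df | Power at 0.05°C |
|---|---|---|---|
| Main effect, 60 v 60 | 0.1 × √(120/4) = 0.548 | 116 | 8.4% |
| Two cells, 30 v 30 | 0.1 × √15 = 0.387 | 58 | 6.7% |
| Interaction | 0.1 / √(4/30) = 0.274 | 116 | 5.8% |

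An omnibus F test over the four groups gives 5.9% to 6.8%, depending on the pattern of means. A one-sided main-effect test gives 13.6%.

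**Step 3: can the planned analysis close the gap?**

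- *Covariate adjustment.* For 80% power on a main effect, the residual SD would have to fall to 0.097. Covariates would then have to explain 1 − (0.097/0.5)² = 96% of the variance. With an illustrative baseline correlation of 0.5 (an assumption), the residual SD is 0.5 × √0.75 = 0.433 and power is 9.6%.
- *Interim analysis.* A single O'Brien-Fleming look at 75% with the overall level held at 0.05 cannot raise power above the fixed-sample figure.

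**Step 4: what 120 participants can detect.** At 80% power, SD 0.5 and two-sided 5%, the figures are 0.26°C for a main effect, 0.37°C for an unadjusted pairwise comparison and 0.52°C for the interaction.

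**Step 5: precision.** The unadjusted 95% confidence interval for a main effect has half-width 1.98 × 0.5 × √(2/60) = 0.18°C, more than three times the stated target.

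**Step 6: if 0.05 is a slip for 0.5.** Then d = 1, and power at N = 120 is above 99.9% for a main effect, 97% for an unadjusted pairwise comparison and 78% for the interaction. By the normal approximation, the interaction needs 16 × 7.849 / 1² = 126 participants for 80%. The interaction comes close, but no contrast gives 120 directly.

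**The case against.** The best defence is that the printed 0.05 is a misprint for 0.5, so that the error lies in the difference and not in the sample size. An ordinary route then leads to 120. Six pairwise comparisons with Bonferroni correction (α = 0.05/6), a difference of 0.5 and SD 0.5 need 27 per group, or 108 in total. A 10% allowance for loss gives 108/0.9 = 120. However, the document states neither the correction nor the allowance. Without the allowance, 30 per group gives 87% power, not 80%. The route is possible but unconfirmed, and the figure in print would still be wrong.

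Three narrower points stand in part:

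- The document shows that difference, SD, power and N are jointly inconsistent. It does not show which of them is at fault.
- The 1°C to 3°C heat loss is a fall within patients, not a difference between groups, so it is background and not proof. The figure of 12,560 likewise depends on applying 0.05°C to a difference of differences.
- A condensed article may leave the powered contrast to the full protocol, so its absence is not a separate fault. It matters here because no choice of contrast rescues the stated calculation.

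The values 0.26°C, 0.37°C and 0.52°C describe what 120 participants can detect. They are not clinically justified targets and should not be presented as such.

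**Conclusion.** The concern holds and must be fixed. On the printed figures, power is about 8% on the most favourable two-sided reading and 6% to 7% for pairwise or omnibus comparisons of the four groups, against a claimed 80%. The shortfall in sample size is at least 20-fold, too large to be rounding or an unstated technical choice. The power figures assume SD 0.5 as printed, equal cells, no loss of participants and no covariate adjustment. Plausible adjustment does not change the conclusion. A slip for 0.5°C is a reasonable explanation, but the document does not establish it, and it would leave open which contrast was powered at 80%.

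**What to change.** The sponsor should confirm the intended difference, the contrast it refers to, the sidedness, and any multiplicity or dropout allowance, and then rewrite the Sample size paragraph for that contrast, keeping N = 120.

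- A factually correct version would say that 120 participants (60 v 60 for each factor) give 80% power at two-sided 5% to detect a main effect of 0.26°C with SD 0.5, and that an interaction is detectable with 80% power only if it is 0.52°C or more. If pairwise comparisons are the target, the unadjusted figure is 0.37°C.
- If 0.5°C was intended, correct the figure and state the resulting power: above 99.9% for a main effect, 97% for an unadjusted pairwise comparison and 78% for the interaction.
- If 0.05°C really is the difference of interest, the paragraph must say that 120 participants cannot detect it with useful power.

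The first two corrections cost one paragraph and no extra patients. In the first, the stated sensitivity becomes less favourable. The third also costs only text, but it means giving up the claim of 80% power at 0.05°C, since meeting that claim would need about 3,140 participants for a two-sided main effect.
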